# Transcutaneous electrical acupoint stimulation to reduce opioid consumption in patients undergoing inguinal hernia repair: protocol for a randomized controlled trial

**DOI:** 10.1186/s13063-022-07019-9

**Published:** 2022-12-29

**Keywords:** Complementary medicine, Pain management, Transcutaneous electrical acupoint stimulation (TEAS), Protocol

## Abstract

**Background:**

The purpose of this study is to evaluate the efficacy and safety of transcutaneous electrical acupoint stimulation (TEAS) in the postoperative treatment of patients undergoing inguinal hernia repair compared with sham and no treatment group.

**Methods:**

This study is a protocol for a three-armed, single-blinded, placebo-controlled randomized controlled trial. Ninety participants scheduled for inguinal hernia repair will be randomly assigned to the TEAS group (*n* = 30), sham group (*n* = 30), and control group (*n* = 30). The TEAS group will receive treatment using four portable coin-sized electro-stimulators at both local and distal acupuncture points. The sham group will receive sham treatment with mock electrostimulation. The treatment groups will receive mixed frequency stimulation (alternating at 2 and 100 Hz every 3 s) in continuous mode for 30 min at intervals of 2 h for 24 h postoperatively. The control group will receive postoperative pain control using patient-controlled analgesia (PCA) device. The primary outcome is the total morphine dose received in the postoperative period (mg) using PCA 24 h after surgery. The number of PCA demands (i.e., times the button will be pressed) and delivered bolus doses, score on the Visual Analogue Scale, opioid-related side effects, the requirement for supplemental medications, score on the Hospital Anxiety and Depression Scale (HADS), and blood levels of stress hormones cortisol and prolactin.

**Discussion:**

The results of this trial will determine whether TEAS with intensified stimulation protocol is a safe and effective option for reducing analgesic consumption and postoperative pain.

**Trial registration:**

ISRCTN76428396. Registered on 05 October 2020. https://www.isrctn.com/ISRCTN76428396

## Background

Patients perceive postoperative pain as one of the most unpleasant aspects of undergoing surgery. Despite numerous arguments supporting the need for effective treatment of postoperative pain, clinical reality is still far from satisfactory [1, 2]. It is reported that nearly half of all surgical patients suffer from persistent postsurgical pain [3]. Inadequate pain management may lead to severe clinical manifestations, including pneumonia, cardiovascular instability, myocardial ischemia, ileus, impaired wound healing, and anxiety [4].

Inguinal hernia repair is characterized by a high intensity of postoperative pain and patient discomfort. Severe pain is associated with tissue trauma and the placement of the preperitoneal mesh. Injury to the vulva, iliohypogastric, and ilioinguinal nerves is the most common cause of pain with a neuropathic component in the pubic and femoral areas [5]. The highest intensity of pain is recorded on the first day after surgery, and one-third of patients complain of moderate or severe pain even 7 days after the repair operation [6].

Opioids, the mainstays of most analgesia regimens during and after surgery, are responsible for dose-related side effects in 12.2% of the time, which delays recovery, incurs higher costs, leads to a longer length of stay, and increases readmission rates [7, 8].

Transcutaneous electrical acupoint stimulation (TEAS) is a non-invasive treatment modality, which combines the effects of transcutaneous electrical nerve stimulation (TENS) with acupuncture point stimulation [9]. TEAS stimulate the afferent nerves at an acupuncture point with low-voltage impulses. Most prior assessments have shown a beneficial effect of TENS or electroacupuncture (EA) in reducing pain intensity after hernia surgery [10–12]. However, to date, there are no randomized controlled trials to evaluate the efficacy of TEAS in the postoperative treatment of patients undergoing inguinal hernia repair.

In this study, for the first time, we will assess the effect of TEAS on opioids consumption in patients undergoing inguinal hernia repair. The trial is also designed to verify whether the analgesic effect of TEAS is associated with the levels of stress hormones.

## Methods and analysis

### Study objective

The primary objective is to evaluate (a) the efficacy and (b) the safety of TEAS in reducing postoperative pain after inguinal hernia repair compared with sham and standard treatment. The secondary objectives include the assessment of pain intensity (Visual Analogue Scale), frequency of complications of opiates (e.g., sedation, pruritus, nausea, vomiting), anxiety and depression (Hospital Anxiety and Depression Scale), and levels of stress hormones (blood levels of cortisol and prolactin).

### Study location

A prospective, three-armed, single-blinded, placebo-controlled randomized controlled trial will be conducted at Wroclaw University Hospital, Wroclaw, Poland. The study was planned in accordance with the Helsinki Declaration to protect the participants and was approved by the ethics committee of Wroclaw Medical University (No. KB-599/2017). The participants will.

be informed on the potential benefits, risks, alternatives, and responsibilities of the study by the researchers during the consent process.

### Study population

Participants will be recruited according to the inclusion, exclusion, and dropout criteria.

Inclusion criteria:Male and female patients aged 18–75 yearsPatients undergoing elective laparoscopic mesh inguinal hernia repairBody mass index 18–30 kg/m.^2^ASA classification I–IIIPatients provide signed informed consent

Exclusion criteria:Patients with bilateral or recurrent inguinal herniaPatients with a history of intolerance, hypersensitivity, or abuse of opioidsUse of opioids in the past monthUse of monoamine oxidase and selective serotonin reuptake inhibitorsPatients wearing a cardiac pacemakerPatients with clinically significant cardiovascular, pulmonary, renal, hepatic, and neurological diseasePatients with skin infections, surgical incision, or scar at the point of application of acupuncturePatients who participated in other clinical trials, or received other acupuncture therapy, in the previous 4 weeksDropout criteria:Patients who have poor clinical compliancePatients who quit the RCT voluntarily will be considered as having dropped out

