### Randomization and blinding

Enrolled participants will be randomly assigned to TEAS, sham, or control group (1:1:1). An independent, blinded statistician will generate the block randomization scheme. The table will be managed by an independent researcher who is not involved in the recruitment, treatment, or assessment. The participants will be blinded to the type of treatment. Mock TEAS will be provided with the same lamplight as real TEAS, so the participants will not be able to predict the allocated group based on the appearance of the treatment (Fig. 1). The practitioners will be aware of the allocation arm while the subjects, outcome assessors, and statisticians performing the data analysis will be blinded to the treatment allocation. The schedule for the study is shown in Fig. 2.

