### Postoperative analgesia

On a patient’s arrival in the postanesthesia care unit, the PCA device will be connected to the patient’s intravenous line and programmed to deliver 1-ml bolus doses of morphine (1 mg) “on-demand,” with a minimal lockout interval of 10 min and a maximum 4-h dose of 15 mg according to a standardized hospital protocol. PCA therapy will be initiated in the postanesthesia care unit when the patient was sufficiently alert to understand and operate the PCA device. If the patient requires pain medication prior to starting PCA therapy, an incremental dose of metamizole 1 g intravenously, will be administered by the postanesthesia care unit nursing staff. The postoperative PCA analgesic therapy will be supplemented with TEAS/sham therapy, which will start when the patient arrives in the postanesthesia care unit.

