Stimulation will be performed using four portable coin-sized electro-stimulators (StimulAid Inc, Poland). A point-detection function in the device will confirm the correct localization of the stimulator. A combination of the LI4 acupuncture point and peri-incisional ashi points will be utilized to augment PCA analgesia in the postoperative period [16–18]. Not only point selection but also the frequency of stimulation and treatment timing play a critical role in determining the outcome of the intervention. Low-frequency (2 Hz) electrostimulation applied at the acupoints exerts antinociceptive effects mainly by enhancing the release of met-enkephalin (M-ENK), β-endorphin (β-EP), and dynorphin [19, 20]. Therefore, the TEAS group will receive mixed frequency stimulation (alternating at 2 and 100 Hz every 3 s) in continuous mode for 30 min at intervals of 2 h [19, 20]. The device will automatically shut off at the end of each 30-min treatment interval. The intensity of the stimulation will be adjusted to each individual to maintain a slight twitching of the regional muscle and achieve De-Qi sensations, such as soreness, distention, and heaviness. In both groups, electro-stimulators will be applied bilaterally to LI4 (He Gu) and ipsilateral to hernia to two ashi points located within a diameter of 5 cm from the incision site (Fig. 3). The sham group will be provided with the same devices as TEAS with the “in use” light flashing in the usual manner; however, the participants will be told that they may not be able to feel the electrical stimulation. The patients in TEAS and sham groups will be told that they are receiving current stimulation. The PCA therapy and TEAS/sham will be discontinued at 24 h.

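### An undefined poor-compliance dropout rule, applicable only after randomisation and by staff who know the allocation, could bias the morphine comparisons with control if dropouts leave the analysis

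*Protocol article*

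**What the plan says.** The Study population section opens with "Participants will be recruited according to the inclusion, exclusion, and dropout criteria" and ends with two dropout criteria, run together in the extracted text: "Patients who have poor clinical compliancePatients who quit the RCT voluntarily will be considered as having dropped out". Poor compliance is therefore a ground for dropout separate from the patient's own decision to leave. The article does not say what has to be complied with, what threshold applies or who decides.

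On timing and staff, Randomization and blinding states "Enrolled participants will be randomly assigned to TEAS, sham, or control group (1:1:1" and "The practitioners will be aware of the allocation arm". The Discussion also concedes, as a limitation, that assessors and medical personnel are not blinded.

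On what each arm must do, the abstract says of the third arm: "The control group will receive postoperative pain control using patient-controlled analgesia (PCA) device". For the other two, Postoperative analgesia says "The postoperative PCA analgesic therapy will be supplemented with TEAS/sham therapy", with TEAS stimulation given "in continuous mode for 30 min at intervals of 2 h". PCA and TEAS/sham both end at 24 h. TEAS intensity is set so that the patient feels it, whereas sham patients are told they may feel nothing.

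The primary endpoint is the total PCA morphine dose in mg.

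**The concern.** Compliance with a treatment given over the 24 h after surgery is observed only once that treatment is under way. The rule therefore acts on patients already randomised, and it lets someone other than the patient classify them as dropped out. Two features make uneven use possible. TEAS and sham patients wear four stimulators on a repeated schedule and control patients wear none. The staff best placed to notice non-compliance know the arm, and no definition limits their judgement.

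The primary outcome does not depend on compliance with the device. A patient who stops stimulation can still use the PCA pump, and the morphine total can still be read to 24 h. If such a patient were left out, an observable outcome would be lost for a reason that may be related to it. The comparison with control would then no longer be between the groups as randomised.

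**Working it through.** **Plan's figures used.** From the sample size section: 30 patients per group and a target reduction of 30% in 24 h PCA opioid. From the statistical section: a 5% significance level, taken as two-sided because the sample size formula uses 1.96. The article gives no compliance rate, dropout rate or SD for morphine, so there is no stated figure to reproduce on this point. (The printed sample size formula gives 1.96² × 0.26 × 0.74 / 0.05² = 295.6, not 30. That is a separate matter and has no bearing here.)

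**Assumptions.** A fraction f = 0.10 or 0.20 of TEAS patients is dropped. Their mean morphine use is δ = 0.5 or 1.0 SD above that of compliers. No control patient is dropped, there is no true effect, and SD / mean (CV) = 0.5.

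**Bias.** Dropping the fraction f lowers the TEAS mean by f × δ in SD units. Multiplying by the CV gives the bias as a share of the mean, and dividing that by 30% gives its share of the target effect. The rejection rate is that of the two-sided 5% t-test, from 20,000 simulated null trials per scenario.

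| f | δ (SD) | TEAS n analysed | Bias (SD) | Bias (% of mean) | Share of 30% target | Null rejection rate |
|---|---|---|---|---|---|---|
| 0.10 | 0.5 | 27 | 0.05 | 2.5% | 8% | 5.4% |
| 0.10 | 1.0 | 27 | 0.10 | 5% | 17% | 6.5% |
| 0.20 | 0.5 | 24 | 0.10 | 5% | 17% | 6.4% |
| 0.20 | 1.0 | 24 | 0.20 | 10% | 33% | 11.0% |

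With all patients kept, the rejection rate was 4.8–5.1%.

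**Check on the last row.** The noncentrality is 0.20 / √(1/24 + 1/30) = 0.20 / 0.274 = 0.73. On 24 + 30 − 2 = 52 degrees of freedom this gives a rejection rate of about 11%, in agreement with the simulation.

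**Second model.** Here k of 30 device-arm patients are dropped, no controls are dropped, and non-compliance has correlation ρ with morphine use (CV 0.5, 40,000 null trials).

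| k | ρ | Bias (% of control mean) | Type I error |
|---|---|---|---|
| 3 | 0 | 0 | 5.0% |
| 3 | 0.3 | −2.8% | 5.6% |
| 3 | 0.5 | −4.7% | 7.0% |
| 6 | 0 | about 0 | 5.1% |
| 6 | 0.5 | −8.5% | 9.8% |

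The two models agree in scale. With ρ = 0 there is no bias, whatever the number removed.

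**Direction.** The sign of δ is an assumption. If the non-compliers are low morphine users, δ is negative and the same sizes count against TEAS.

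**TEAS versus sham.** Both arms wear the same device at the same points. With k = 3 and ρ = 0.5 in both, the bias between them is 0. A bias here needs another route: felt versus unfelt stimulation, or the judgement of unblinded staff.

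**The case against.** The strongest objection is that the decisive step is not in the text. The article says such patients count as dropped out. It does not say that their morphine data are discarded, that follow-up stops or that they are replaced. Analysis populations are commonly set out in a full protocol or SAP, neither of which is shown. This stands, and it makes the point conditional. It does not dispose of it, because the article itself fixes the rule and exclusion is the ordinary meaning of dropping out.

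A reader might infer that the rule certainly removes more TEAS than control patients and favours TEAS. The documents do not support this, for three reasons:

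- The criterion is not limited to the device. Control patients can also fail on PCA use, pain scores, HADS or blood sampling.
- The device burden may be light: "The device will automatically shut off at the end of each 30-min treatment interval", intensity is set individually, and the Discussion describes the modality as automatic and comfortable. No source supports 10–20% non-compliance.
- Patients in distress might remove the stimulators, but so might comfortable patients who see no need for them. The direction is open.

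It is also fair that three of the four scenarios give only 5.4–6.5% rejection. The 11% figure belongs to the extreme corner.

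**Conclusion.** The concern holds as a conditional one. The article sets an undefined compliance criterion that can only act after randomisation. The practitioners are unblinded, and only two of the three arms have stimulators to comply with. Bias in the comparisons with control needs three things together: exclusion of dropouts from the analysis, unequal removal, and a link between non-compliance and morphine need. The article documents none of the three.

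If all three hold at the assumed values, the bias is 0.05–0.20 SD (2.5–10% of the mean) and the type I error is 5.4–11%. If the link is absent, the bias is zero. The device-versus-no-device argument does not reach TEAS versus sham.

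This should be fixed, with moderate confidence. It does not show that the trial's result is biased.

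**What to change.** Do not use poor compliance as a reason to drop a randomised patient from the comparison. State that every randomised patient with PCA data is analysed in the assigned arm, using the PCA record to 24 h. Limit dropout to withdrawal of consent for data use. Report the number of patients classed as non-compliant in each arm, with reasons. Use compliance only to define a supportive per-protocol analysis.

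The Trial status section says recruitment was completed on 31/12/2020, so a change to the criterion cannot alter how patients were handled. The change belongs in analysis and reporting, and the PCA records of any patients dropped for compliance should be recovered where they exist.

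The cost is a few sentences, one extra line per arm in the participant flow, and some record retrieval. The downside is a slightly diluted effect estimate, because patients who stopped stimulation still count in their arm.

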### Endpoints

#### Primary endpoint

Total morphine dose received in the postoperative period (mg) using patient-controlled analgesia (PCA) device.

#### Secondary endpoints

The number of PCA demands (i.e., times the button will be pressed) and delivered bolus doses after surgery will be assessed. Score on the Visual Analogue Scale prior to the surgery and at 4, 8, 12, 16, and 20 h after surgery will be recorded. The scale of 0 to 10, where 0 represents the complete absence of pain and 10 represents the worst pain intensity. Moreover, opioid-related side effects and the requirements for supplemental medications (e.g., antiemetics, antipruritics, and analgesics) will be recorded during the postoperative observation period.

The Hospital Anxiety and Depression Scale (HADS) will be used to evaluate the depression and anxiety before and at 24 h after surgery. Blood levels of stress hormones cortisol and prolactin will be measured at the same time points.

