### Sample size justification

Power analysis was performed to determine the number of patients per group sufficient to.

detect a decrease of 30% or more in the PCA opioid analgesic requirements during the first 24 h after surgery, based on the results of the previous studies [13–15]. Each group will include 30 participants, a total of 90 participants. The proper size of the sample was calculated using the following formula:$$Sample\;size=\frac{Z_{1-a/2}{^2}p\left(1-p\right)}{d^2}$$

where:*Z*_1_ − _*a*/2_ is the standard normal variate (at 5% type 1 error *p* < 0.05), − 1.96;*p* is the expected prevalence obtained from a pilot study, − 0.26; and *d* is the absolute precision, − 0.05.

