### Statistical analysis

Quantitative variables will be reported using the mean and SD (M ± SD) for normally distributed data or median (Me), the lower quartile (Q1), and the upper quartile (Q3) and the range (Min–Max) for skewed data. Kolmogorov–Smirnov Normality Test will be used to verify the normality of distributions. Intergroup differences between the average values of the quantitative data will be assessed using the Student’s *t*-test (*t*-test for independents samples by groups) or Mann–Whitney *U* test. Kruskal–Wallis ANOVA will be used for multiple comparisons (post hoc tests). Additionally, a multivariate analysis, ANOVA for factorial designs (Factorial ANOVA), will be performed to analyze the main effects and their interactions (relationships between independent variables). Qualitative variables (nominal) will be represented as (*n*) and proportions (%). Independence of qualitative variables from the patient status will be verified by the chi-square test or Fisher’s exact test. The significance level will be set at 5%. All data will be analyzed using the Statistica v.13.3 (StatSoft).

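### Pain on the VAS is scored before surgery and five times after it, but every method the article names for quantitative data assumes independent observations, and none is stated to use the preoperative score

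*Protocol article*

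**What the plan says.** Under Study objective, VAS is placed among the secondary aims: "The secondary objectives include the assessment of pain intensity (Visual Analogue Scale". Secondary endpoints gives the schedule: "Score on the Visual Analogue Scale prior to the surgery and at 4, 8, 12, 16, and 20 h after surgery will be recorded". Each patient therefore contributes one preoperative and five postoperative scores.

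Statistical analysis gives one list of methods for all quantitative variables and does not link any of them to a particular endpoint:

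- Differences between groups are to be "assessed using the Student’s *t*-test (*t*-test for independents samples by groups) or Mann–Whitney *U* test".
- For comparisons among several arms, the section adds a Kruskal–Wallis analysis followed by post hoc testing.
- "ANOVA for factorial designs (Factorial ANOVA), will be performed to analyze the main effects and their interactions". The factors to be crossed are not named.

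The significance level is 5%. The section names no within-patient factor, per-patient summary or principal VAS time. On group size: "Each group will include 30 participants, a total of 90 participants".

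**The concern.** Five scores from one patient are correlated, and the listed methods have no place for that correlation. They can be applied to the VAS schedule in two obvious ways, and each has its own problem.

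- **Testing at each time.** Each test uses one score per patient and is valid at 5%. The problem is multiplicity: five times and three pairs of arms give up to 15 tests, with no statement of which one counts.
- **Pooling the scores in a factorial ANOVA.** The trial randomises one factor with three levels, so time is an obvious candidate for the second factor. If time is entered as a between-patient factor, 90 patients are analysed as 450 independent observations. This is pseudo-replication.

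In addition, no listed method is stated to use the preoperative VAS as a covariate.

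The objective and the anticipated conclusion both speak of reducing postoperative pain, and VAS is the direct measure of pain intensity. A chance VAS difference could be read as supporting that part of the conclusion. The primary endpoint is one total morphine dose per patient and is not affected.

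**Working it through.** **Inputs from the article.** Three arms, 30 patients per arm, five postoperative times, 5% level. That gives 3 × 5 = 15 arm-by-time cells, 15 × 30 = 450 scores, and 450 − 15 = 435 residual degrees of freedom if all scores are treated as independent.

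**Assumptions, not in the article.** Two-sided tests, normal data, no treatment effect, and a within-patient correlation ρ. Results are given for ρ from 0 to 0.9 with equal correlation between all times (20,000 simulated trials per setting). A first-order autoregressive pattern gave similar ranges.

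**The article's own figure.** The only error rate it states is 5%. One t-test at one time with 30 per arm reproduces it: 4.7–5.2% in every setting.

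**Testing at each time.** With five independent tests, the chance of at least one false positive is 1 − 0.95^5 = 22.6%. Positive correlation lowers it. By simulation:

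| ρ | One pair of arms, 5 tests | All three pairs, 15 tests | Three-group test at each time, 5 tests |
|---|---|---|---|
| 0 | 22.3% | 47.6% | 22.2% |
| 0.3 | 21.3% | 44.9% | 21.3% |
| 0.5 | 18.4% | 39.8% | 18.7% |
| 0.7 | 15.1% | 32.8% | 15.3% |
| 0.9 | 10.4% | 23.4% | 10.6% |

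The last column used the ordinary F test on normal data, as a stand-in for Kruskal–Wallis.

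**Factorial ANOVA with time between patients.** Let σ² be the variance of one score.

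- *Group effect.* The model takes the variance of an arm mean to be σ²/(5 × 30). The true value is σ²(1 + 4ρ)/(5 × 30), so F is inflated by about 1 + 4ρ. The 5% critical value of F with 2 and 435 degrees of freedom is 3.016. With 2 numerator degrees of freedom, the false-positive rate is close to exp(−3.016/(1 + 4ρ)):
  - ρ = 0.3: exp(−3.016/2.2) = 25.4% (simulated 25.8%)
  - ρ = 0.5: exp(−3.016/3.0) = 36.6% (simulated 36.8%)
  - ρ = 0.7: exp(−3.016/3.8) = 45.2% (simulated 45.4%)
  - Full simulated range for ρ from 0 to 0.9: about 5% to 52%.
- *Group-by-time interaction.* Here F is deflated by about 1 − ρ. The simulated rate is 0.4% at ρ = 0.3 and about 0% at 0.5 and above. A real change in effect over time would be hard to detect.

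**One summary per patient.** Comparing each patient's mean of the five postoperative scores gives 4.7–5.2% at every ρ, for the three-group F test and for one pairwise t-test. This was run without the baseline covariate.

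**The case against.** The strongest reply is that the article does not describe either of these analyses. The list is generic. It does not say that VAS will be tested at each time, that 15 tests are planned, or that time is a factor in the ANOVA. The factorial ANOVA could equally cross arm with a baseline characteristic such as hernia type, which involves no pseudo-replication. This is correct. A reader might infer that the plan carries a fixed false-positive rate of 15–45%. The documents do not support that, because the rates depend on an unstated application and an unstated correlation.

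A second reply is that the VAS model and any multiplicity rule for a secondary endpoint may sit in an analysis plan that is not shown. This also stands, so the absence of such detail is not the point. The point is that the article does commit to a list of methods, and the list does not suit an outcome it schedules six times.

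Other stronger readings also fail:

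- That only two-sample tests and a factorial ANOVA are offered. Kruskal–Wallis with post hoc tests is listed too. A three-group test at each time gives about 15–21% (ρ 0.7 to 0.3), well below the rate for 15 ungated pairwise tests. It does not handle repeated scores either.
- That ignoring correlation inflates every analysis. It inflates only the pooled group effect. In per-time testing, correlation lowers the overall rate.
- That a false VAS finding is likely. Every per-time rate above is below 50%, and the TEAS-versus-sham rate is 15–21%.
- That VAS is the leading secondary endpoint. The article does not rank them.

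Finally, a mixed model is not the only remedy. Bonferroni over five times (0.01 each) gives 1 − 0.99^5 = 4.9% for one pair if the tests are independent, and less if they are positively correlated.

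**Conclusion.** The point holds in a limited form. The methods the article names for quantitative data do not fit the VAS schedule it sets: all assume independent observations, and none is stated to use the preoperative score.

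The size is conditional on how the methods are applied. Under per-time testing, the chance of at least one false positive is about 15–21% for TEAS versus sham and 33–45% for all 15 pairwise tests at ρ from 0.7 to 0.3; taking both together, it is about 10–48% over ρ from 0 to 0.9. Under a factorial ANOVA with time between patients, the group effect is falsely significant in about 25–45% of trials at ρ from 0.3 to 0.7, while the interaction test is very conservative. The correlations are assumed, and the article does not say which route will be taken.

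The point concerns a secondary endpoint. It should be corrected, but it does not touch the morphine analysis.

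**What to change.** For postoperative VAS, replace the listed methods with one of:

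- a linear mixed model with arm, time, arm-by-time and preoperative VAS as covariate, with repeated measures within patient; or
- an ANCOVA of each patient's mean VAS over 4–20 h on preoperative VAS, if the software is limiting.

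Name TEAS versus sham, averaged over 4–20 h, as the single principal VAS contrast. Show differences at each time descriptively, with confidence intervals.

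The change is to the wording of the analysis and needs no new data. The cost is that significance claims at single times are given up. Trial status reports that recruitment ended on 31/12/2020, so the choice should be documented before any unblinded analysis, or labelled post hoc if that analysis has already been done.

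### The 24-h cortisol and prolactin draw takes its clock time from the operating list, and the stated unadjusted tests leave that variance in: a possible precision loss on a secondary endpoint

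*Protocol article*

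**What the plan says.** Under Secondary endpoints, the protocol article has HADS assess "depression and anxiety before and at 24 h after surgery". The hormones take over that schedule: "Blood levels of stress hormones cortisol and prolactin will be measured at the same time points". Each patient thus gives one preoperative and one postoperative sample. The postoperative sample is fixed relative to surgery, not to the clock, and the preoperative sample is not timed at all.

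The hormones have two roles. Study objective lists among the secondary objectives "levels of stress hormones (blood levels of cortisol and prolactin". The Background adds a second aim, to "verify whether the analgesic effect of TEAS is associated with the levels of stress hormones".

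On analysis, Statistical analysis states: "Intergroup differences between the average values of the quantitative data will be assessed using the" t-test or the Mann–Whitney test. Kruskal–Wallis serves for multiple comparisons. It also plans an "ANOVA for factorial designs (Factorial ANOVA), will be performed to analyze the main effects and their interactions", without naming the factors. No baseline or clock-time adjustment is named for the hormones. Allocation is by blocks: "Enrolled participants will be randomly assigned to TEAS, sham, or control group (1:1:1". On size: "Each group will include 30 participants, a total of 90 participants".

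**The concern.** A draw 24 h after surgery falls at about the hour at which that patient's operation ended. (The text says only that it is after surgery; taking the end of the operation as the anchor is an inference.) Cortisol varies over the day, and prolactin may too. This is general physiology and not something the documents state. If so, a patient's place on the operating list shifts the 24-h value for reasons unrelated to stress or treatment.

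Three uses of the data are affected differently:

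- **Comparison of arms at 24 h.** List position adds variance that an unadjusted test leaves in the error term.
- **Before-after change within an arm.** If the preoperative sample is drawn at a different hour from the 24-h sample, the change contains a time-of-day component that can pass for a stress response.
- **Association of analgesic effect with hormone level.** This is not a comparison of randomised groups. If operating time is also related to morphine use or pain, it confounds the association. If it is not, it only blurs it.

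At stake are the precision of one secondary comparison and the interpretation of the association aim. The primary endpoint is untouched.

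**Working it through.** The plan gives no variance, effect size or power for the hormones, so there is no figure of its own to reproduce on this point. From the documents come 30 patients per arm, 1:1:1 randomisation, a 5% significance level and the two sampling times. Everything else below is assumed and shown as a range.

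**1. Share of the 24-h cortisol variance due to clock time.** Assume cortisol falls linearly at 10–30 nmol/L per hour, operations end uniformly over a 4–8 h span, and the SD from all other sources is 100–130 nmol/L.

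- Clock-time SD: s = slope × span / √12
- Share of variance = s² / (s² + SD²)
- Extra patients that would buy the same precision as adjusting = share / (1 − share) = s² / SD²

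| Case | Slope | Span | Other SD | s | Share | Extra patients |
|---|---|---|---|---|---|---|
| Low | 10 | 4 h | 130 | 11.5 | 133/17,033 = 0.8% | 0.8% |
| Middle | 20 | 6 h | 100 | 34.6 | 1,200/11,200 = 10.7% | 12% |
| High | 30 | 8 h | 100 | 69.3 | 4,800/14,800 = 32.4% | 48% |

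**2. Effect on power and type I error.** A second model used a 24-h cosine rhythm and 8,000 simulated trials per scenario, with end of surgery uniform over a 4-h or 8-h list and a pre/post correlation of 0.5. Units are the non-rhythm SD. The true effect was set at the difference that 30 v 30 detects with 80% power in the normal approximation: (1.96 + 0.84) × √(2/30) ≈ 0.72 SD. With no rhythm, the simulated unadjusted test has power of about 0.78.

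| Rhythm amplitude | List | Rhythm SD in 24-h value | Power, unadjusted | Power, clock time as covariate |
|---|---|---|---|---|
| 0.5 | 4 h | 0.11 | 0.78–0.79 | 0.77–0.78 |
| 0.5 | 8 h | 0.26 | 0.75–0.77 | 0.77–0.79 |
| 1.0 | 4 h | 0.21 | 0.77 | 0.78 |
| 1.0 | 8 h | 0.52 | 0.68–0.69 | 0.78 |
| 1.5 | 4 h | 0.32 | 0.75–0.76 | 0.78 |
| 1.5 | 8 h | 0.79 | 0.57–0.58 | 0.77 |

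Type I error of the unadjusted test stayed at 0.045–0.054 in every scenario, so arms are not biased against each other.

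**3. What the preoperative sample can do.** A 24-h interval brings the second draw back to the same point of the daily cycle as the operation.

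- If the first draw comes shortly before surgery (1.5 h before its end in the model), the rhythm SD left in the change score is only 0.05–0.16. Power is then 0.77–0.80 for change from baseline and 0.81–0.88 for ANCOVA on baseline.
- If every first draw is at a fixed 07:00, the change score keeps the full rhythm SD. At amplitude 1.5 on an 8-h list, power is 0.58 for change and 0.65 for ANCOVA on baseline alone, against 0.77 with clock time as the covariate.

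The text does not say which of these applies. Baseline and clock time were examined as separate covariates, not jointly.

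**4. Within-arm change.** Under the slopes in step 1, each hour by which the clock times of the two draws differ adds 10–30 nmol/L of pure time of day to the change. The size in this trial cannot be stated, because the preoperative draw is untimed.

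**The case against.** The strongest reply is that a condensed article need not give a draw window or a covariate for a secondary laboratory endpoint. These may stand in the full protocol or analysis plan, which are not shown, and factors left unnamed in the factorial ANOVA are not thereby excluded. This stands as a limit on confidence. What remains is that the article does fix the schedule and does name the between-group tests, and those tests as named are unadjusted.

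A second reply is that the size rests wholly on assumptions, and that an answer running from 1% to 32% does not show that the problem matters here. That also stands. Operating hours are not given, on a 4-h list the loss is hardly visible, and prolactin has no figure at all.

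A reader might infer more than this in three ways, and the documents do not support any of them:

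- **That daily rhythm confounds the comparison of arms.** Operating time is balanced by randomisation in expectation, and the simulated type I error is nominal.
- **That nothing in the design can remove the rhythm.** The 24-h interval, with a preoperative sample drawn shortly before surgery, would cancel most of it. The safeguard is available, but the article neither times that sample nor commits to using it.
- **That a spurious fall will be reported as a stress response.** Such a fall depends on an earlier preoperative draw and is common to all arms. The article describes tests between groups and plans no within-arm hormone test.

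Moving both draws to one fixed morning hour is also tempting, but it is a trade-off. Hours since surgery would then vary between patients, and the sample would no longer coincide with the 24-h HADS or with the end of PCA and stimulation. Recruitment closed on 31/12/2020 in any case.

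**Conclusion.** The point holds as a minor one, with low confidence. The clock time of the 24-h hormone draw follows the operating time, and the stated between-group tests have no term for baseline or clock time.

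For the comparison of arms the consequence is possible loss of precision, not bias. Clock time is about 1–32% of the 24-h cortisol variance, worth 1–48% more patients, if cortisol falls 10–30 nmol/L per hour, operations end over 4–8 h and the other SD is 100–130 nmol/L. Power drops clearly (from about 0.78 to 0.57–0.69) only with an 8-h list and a rhythm amplitude of at least 1 SD. All these inputs are assumptions.

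The association aim in the Background is the more exposed use, since randomisation does not protect it. Its size cannot be given, because nothing in the documents shows whether operating time is related to morphine use or pain.

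**What to change.** In the analysis of cortisol and prolactin:

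1. Compare arms on the 24-h value by ANCOVA, with the preoperative value and the clock time of the 24-h draw as covariates, on a log scale if the values are skewed.
2. Take the clock time from the recorded draw time or, failing that, derive it from the operation record.
3. Use the same adjustment when relating analgesic effect to hormone level.
4. Do not interpret the raw before-after change within an arm as a stress response.

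The cost is one or two covariates in models for a secondary endpoint with 30 patients per arm. The preoperative value is already collected under the stated schedule, and no sampling changes. If the list proves short, the clock-time term gains little and costs almost nothing: with no rhythm at all, the simulated power was 0.78 with or without it. If the full protocol or analysis plan already specifies these covariates, no change is needed.
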